### 11.2 STATISTICAL HYPOTHESES

The null hypothesis assumes that proportion of subjects randomized to study treatment achieving a primary endpoint (p) is lower than proportion in placebo group (p0):

$$H_0: p - p_0 \leq \delta$$

$$H_a: p - p_0 > \delta,$$

where  $\delta$  is a non-inferiority margin (-15%).

### 11.3 SAMPLE SIZE DETERMINATION AND PLANNED RECRUITMENT RATES

Due to nature of this study (proof of concept phase II trial), with effect size being unknown, following assumptions were made:

- Proportion of subjects randomized to receive IMP achieving primary endpoint will be 40% and this proportion will be identical in a placebo group
  - A non-inferiority margin  $\delta$  will be equal to 15%
  - One sided significance level 0.2
  - Power of 70%
  - One interim analysis (with Hwang-Shih-DeCani  $\alpha$  pending function)
  - A drop-out rate of 10%.
- Taking these into consideration, a minimal number of subjects per group is 46 – so 92 subjects in each study arm.

Sample size calculations were made in R version 3.6 using gsDesign library version 3.1.1.

## 11.4 POPULATIONS FOR ANALYSES

### 11.4.1 INTENT TO TREAT POPULATION (ITT)

A subset of all enrolled subjects consisting of subjects that were randomized independently of the fact if they have received study treatment. This population will be used for baseline characteristics and efficacy analysis.

### 11.4.2 PER PROTOCOL POPULATION (PP)

A subset of ITT population consisting of subjects that have functional status assessed with modified Rankin scale at 90 days (+/- 3 days) after study treatment administration. This population will be the main population used for efficacy analysis.

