n – Preparation of the study treatment should be initiated immediately after receipt of the laboratory test results of anti-IIa or anti-Xa activity  $>50$  ng/mL or dabigatran concentration for the respective arm of the study. However, in patients on dabigatran, it is possible to enrol such a subject into the study based solely on a patient's or witness' report on the last intake of the anticoagulant ie, when it was administered within the last 24 hours preceding initiation of the study treatment. The procedure is described in the Laboratory Manual.

o – Infusion of the thrombolytic component of the study treatment (rtPA or corresponding placebo) should be initiated within 4.5 hr from the AIS onset, but **no later than within 6 hours from AIS onset**, otherwise participant should be withdrawn from the study.

p – In case of initiating thromboembolic prophylaxis, i.e., starting antiplatelet agents, heparins or OAC/NOAC, the information about type of medication, dosage and time of initiating treatment should be entered in patient's medical records and on eCRF (see [Section 7.6.1](#))

q – In women of childbearing potential urine pregnancy test must be performed or a blood pregnancy test if urine cannot be obtained. Females of childbearing potential and women in a postmenopausal state: females of childbearing potential and women with no menses for a period < 12 months must have a negative pregnancy test at Visit 0 and have to agree not to start a pregnancy from the signature of the informed consent up to the Final Visit, using an appropriate birth control method such as combined oestrogen-progestin containing hormonal contraceptives (e.g., oral, injectable, transdermal), progestin-only hormonal contraceptives (e.g., oral, injectable, implantable), intrauterine device (IUD) or intrauterine hormone-releasing system (IUS) in combination with male condom, bilateral tubal occlusion, vasectomised partner, sexual abstinence.

**Woman of childbearing potential (WOCBP):** i.e., fertile, following menarche and until becoming post-menopausal, unless permanently sterile. Permanent sterilization methods include hysterectomy, bilateral salpingectomy and bilateral oophorectomy.

**Postmenopausal state** is defined as no menses for 12 months without an alternative medical cause.

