### 5.4 SCREEN FAILURES

Due to the critical impact of time elapsed from the AIS onset to initiating IVT, the intensity of standard diagnostic procedures, and the possibility of changes in patient's medical condition over time, the final confirmation (verification) of eligibility to receive the study treatment will take place just prior initiating study treatment. Therefore, screen failures are defined as patients who signed the ICF to participate in the clinical trial (enrolled patients) but were not:

- randomized, or
- did not receive study treatment

due to not meeting all the inclusion criteria or meeting any of the exclusion criteria along screening and/or diagnostic procedures required before study treatment administration.

These participants should have the reason for screen failure / study withdrawal recorded in the eCRF as “eligibility criteria not fulfilled”.

A minimal set of screen failure information is required to ensure transparent reporting of screen failure participants to meet the Consolidated Standards of Reporting Trials (CONSORT) publishing requirements and to respond to queries from regulatory authorities. Minimal information includes demography, screen failure details, eligibility criteria, and any SAEs.

The enrolment and randomisation process are described in [Section 6](#).

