### 6.3.4 ELIGIBILITY

Due to critical impact of time from AIS onset to IVT initiation, final verification of participant's eligibility (all inclusion and exclusion criteria verified) will take place after randomisation and before initiating study treatment administration.

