### 11.4.3 SAFETY ANALYSIS POPULATION (SAF)

A subset of intent to treat analysis population consisting of subjects that received study treatment. This population will be used for all safety analyses.

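### The main efficacy set is a complete-case set labelled per protocol, and the follow-up rules do not secure day-90 outcomes for the all-randomised set

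*Protocol*

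**What the plan says.** **Analysis sets (Protocol 11.4).** The ITT set in 11.4.1 is described as "consisting of subjects that were randomized independently of the fact if they have received study treatment", and "This population will be used for baseline characteristics and efficacy analysis". The per-protocol set in 11.4.2 is "A subset of ITT population consisting of subjects that have functional status assessed with modified Rankin scale at 90 days (+/- 3 days"; the days are counted from study treatment administration. Of this set the section says "This population will be the main population used for efficacy analysis". The safety set in 11.4.3 is "A subset of intent to treat analysis population consisting of subjects that received study treatment".

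**What happens between randomisation and treatment.**
- Section 6.3.4 says that final verification of eligibility "will take place after randomisation and before initiating study treatment administration". Section 6.4.3 asks the investigator to confirm at randomisation that all eligibility criteria are met.
- Section 5.4 counts as screen failures those consenting patients who were randomised but not treated because they proved ineligible. For them, "Minimal information includes demography, screen failure details, eligibility criteria, and any SAEs".
- Section 1.3, note o, gives 6 hours from onset as the latest start for the thrombolytic component or its placebo, "otherwise participant should be withdrawn from the study". Note m asks the investigator to consider withdrawal if randomisation came later than 3.0 hours.
- Section 8.1 goes the other way: a patient whose study treatment is ended early, for any reason, is still evaluated at days 2, 7, 30 and 90.

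**The concern.** A per-protocol set normally restricts to patients who were eligible, were treated as planned and had no major deviation. The set in 11.4.2 restricts on something else: whether a day-90 score exists inside a seven-day window. That is selection on an event after randomisation, and it governs the primary test. A score taken on day 94 would be lost although it is informative.

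The ITT set would be the natural safeguard, but it needs outcomes. The screen-failure and withdrawal rules allow a randomised patient to leave without a day-90 mRS. The visit schedule adds to this: section 1.3, note c, counts every visit from the start of the thrombolytic or its placebo, so an untreated patient has no defined day 90. An SAP can choose sets and imputation methods, but it cannot recover outcomes that were never collected.

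The primary test is one of non-inferiority at a lenient one-sided level, so losing poor outcomes from the active group moves the result towards success.

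**Working it through.** **1. The sets side by side.**

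| Question | ITT (11.4.1) | PP (11.4.2) |
|---|---|---|
| Who is in? | All randomised, treated or not | ITT patients with an mRS in the day-90 window |
| Adherence, eligibility or deviation criterion? | No, as expected | None stated |
| Out-of-window score? | Patient stays in | Patient excluded, read literally |
| Role | Baseline and efficacy | Main efficacy set |

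The PP column describes complete cases.

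**2. The routes out after randomisation.**

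| Patient | Rule | Day-90 mRS required? |
|---|---|---|
| Randomised, then ineligible and untreated | 5.4: screen failure, minimal data | No |
| Randomised, thrombolytic or placebo not started by 6 h | 1.3 note o: withdrawn from the study | No |
| Treatment begun and stopped | 8.1: stays in follow-up | Yes |

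The first two rows do not fit the ITT definition, which includes these patients. Their direction is opposite to 8.1.

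**3. The plan's own sample size.** Inputs from 11.3: 40% in both groups, margin 15 points, one-sided alpha 0.20, power 70%, 10% drop-out, one interim look with Hwang-Shih-DeCani spending.

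n = 2 × 0.40 × 0.60 × (0.8416 + 0.5244)² / 0.15² = 39.8, so 40 per group; 40 / 0.90 = 44.4, so 45. Two-look variants (spending parameter −4, with or without an assumed futility bound) give 44.5 to 47.0. The stated 46 therefore reproduces, and this point does not affect it. The parameter −4 also gives an interim level of 0.20 × (1 − e²)/(1 − e⁴) = 0.0238, as in 11.5.4.1.

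**4. Illustration of what complete-case selection can do.** Assumptions not in the document: true all-randomised rates of 25% active and 40% placebo (exactly at the margin), and every missing active patient a non-responder. I take 46 per group from 11.3 and the final level 0.176 from 11.5.2.1 (z = 0.931). The calculation uses the normal approximation and the final test only.

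With m active patients missing: p_A = 0.25 × 46/(46 − m); d = p_A − 0.40; SE = √[p_A(1 − p_A)/(46 − m) + 0.24/46]; chance of declaring non-inferiority = Φ((d + 0.15)/SE − 0.931).

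| m | p_A | d (points) | False non-inferiority |
|---|---|---|---|
| 0 | 0.250 | −15.0 | 17.6% |
| 2 | 0.261 | −13.9 | 20.8% |
| 3 | 0.267 | −13.3 | 22.5% |
| 4.6 (10% of 46) | 0.278 | −12.2 | 25.7% |

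Worked row, m = 2: p_A = 11.5/44 = 0.2614; SE = √(0.004388 + 0.005217) = 0.0980; Φ(0.01136/0.0980 − 0.931) = Φ(−0.815) = 0.208.

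**5. The direction is not given.** If instead 4.6 placebo non-responders were lost, p_P = 0.40/0.90 = 0.444, d = 0.25 − 0.444 = −19.4 points, SE = 0.1002, and the chance falls to Φ(−0.0444/0.1002 − 0.931) = 8.5%. If 4.6 non-responders were lost from each group, d = −0.15/0.90 = −16.7 points, again away from success.

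**The case against.** **A reader might infer that no analysis set preserves the randomisation.** The text does not support that. Section 11.4.1 defines an all-randomised set and assigns it to efficacy. Nor do 11.4.1 and 11.4.2 contradict each other on rank: PP is main, and ITT is the other efficacy set.

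**A reader might infer that the PP set keeps untreated patients and so dilutes harm.** That is not supported either. The window in 11.4.2 runs from treatment, and untreated patients who leave under 5.4 or note o need not have the score that would admit them. Only treated patients with deviations are clearly kept.

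**The exits are narrow and blinded.** Section 5.4 covers untreated patients only when the reason is ineligibility, never says that they leave ITT, and sets a minimum of data. Sections 6.4.1 and 6.4.3 place randomisation after the assay result (with the dabigatran exception) and after eligibility has been confirmed, so such patients should be few. Investigators are blinded, and exclusions made blind on baseline facts need not favour either group. This stands as a limit on the size of the problem. It does not remove the conflict between the passages.

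**The SAP may settle it.** Section 11.1.2 leaves detailed population rules to the SAP, and imputation and sensitivity analyses belong there. Death is scored mRS 6 in 9.1.2, so deaths need not be lost. All of this is fair. Still, the protocol itself names the main set, and it is the protocol's follow-up rules that decide which outcomes exist.

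**All-randomised primacy is debatable in a non-inferiority test**, because untreated patients pull the groups together. This stands, and is why a co-main per-protocol set is offered.

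**Conclusion.** The point holds in limited form. The main efficacy set is a complete-case set under a per-protocol label. The set that preserves the randomisation is defined but is not main, and the rules in 5.4 and 1.3 note o can leave it without outcomes, contrary to 8.1 and 11.4.1.

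The size of any bias is unknown. The rise from 17.6% to about 21–26% rests on assumed true rates at the margin, loss of active-group non-responders only, and a normal approximation; other loss patterns work the other way.

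A reader might infer larger figures by starting from equal 40% rates: 0.40/0.90 − 0.40 = 4.4 points, or 0.40/0.90 − 0.30/0.90 = 11.1 points with opposite extremes in the two groups. Those are extreme scenarios placed where non-inferiority is true. At 25% against 40% the first assumption gives 0.25/0.90 − 0.25 = 2.8 points. The documents supply no reason to expect either extreme.

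This should be fixed. It concerns the primary analysis, and the remedy depends on data that must be collected while patients are in the trial, but an all-randomised efficacy set already exists in the plan.

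**What to change.** 1. In 11.4, make the all-randomised set the main efficacy set, or co-main with a genuine per-protocol set defined by eligibility, treatment received and absence of major deviations.
2. Rename the present PP set complete cases and keep it as supportive.
3. State that deaths count as mRS 6 and that the mRS nearest day 90 is used, with the ±3-day window only as a deviation flag.
4. In 5.4, limit screen failure to patients who were not randomised. Reconcile 6.3.4 with 6.4.3 on when eligibility is settled.
5. Reconcile 5.4 and 1.3 note o with 8.1 and 11.4.1, so that every consenting randomised patient has a day-90 mRS, counted from randomisation if untreated.

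No treatment rule or time limit for treatment changes; only follow-up and analysis do. Imputation and tipping-point details can stay in the SAP.

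The cost is amendment wording and a few extra day-90 contacts. Section 6.5.6 allows a telephone visit only in exceptional situations, so the amendment should say whether untreated patients qualify. The all-randomised set also brings some dilution from untreated patients, which the per-protocol set addresses.

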### 11.4.3 SAFETY ANALYSIS POPULATION (SAF)

A subset of intent to treat analysis population consisting of subjects that received study treatment. This population will be used for all safety analyses.

## 11.5 STATISTICAL ANALYSES

### 11.5.1 GENERAL ASSUMPTIONS

#### 11.5.1.1 STATISTICAL SIGNIFICANCE ASSUMPTIONS

Statistical significance level will be equal to 0.20 for purpose of primary endpoint analysis and 0.05 otherwise. P values  $\geq 0.001$  will be reported to 3 decimal places; p-values less than 0.001 will be reported as “<0.001”. The mean, standard deviation, and any other statistics other than quantiles, will be reported to one decimal place greater than the original data. Quantiles, such as median, or minimum and maximum will use the same number of decimal places as the original data. Estimated parameters, not on the same scale as raw observations (e.g. regression coefficients) will be reported to 3 significant figures.

#### 11.5.1.2 BASELINE DESCRIPTIVE STATISTICS

Age, sex, NIHSS, mRS, and Barthel index will be presented for Visit 0 overall and for each treatment arm and treatment group (study treatment and placebo).

#### 11.5.1.3 TABULATION OF INDIVIDUAL PARTICIPANT DATA

Data will be listed as documented. Relevant generated and transformed variables will be listed next to the original data items. Any imputed value will be flagged.

In all listings the patient identifier and the randomized treatment group will be included. The patient identifier consists of the study centre and the patient number, additionally a flag specifying analysis set will be provided.

In general, patient listings will be sorted by patient identifier and visit (if applicable), unless otherwise stated.

Patient listings of data that is collected independently from visits (e.g., adverse events, medical histories, or medication) will be sorted by patient identifier, day of onset or start day of administration, duration and MedDRA preferred term or WHO base substance name, respectively.

Missing values in the listings will be represented as NA (not available) for both text and numerical data. In case of partially missing dates (when day or day and month is unknown) missing data will be represented as series of 9s – for example 2017-05 will be presented as 2017-05-99. Any imputed data will be presented separately from raw data or flagged accordingly to be able to review all data as collected.

---

## 11.5.2 EFFICACY ANALYSES

---

### 11.5.2.1 ANALYSIS OF THE PRIMARY ENDPOINT

Primary endpoint analysis for each study arm (dabigatran, apixaban, or rivaroxaban) will be performed independently. Proportion of subjects achieving primary endpoint for active treatment and placebo as well as difference of proportions together with 82% Confidence Interval (CI) will be calculated. One-sided noninferiority test with 15% margin for difference in proportions will be performed. A p value lower than 0.176 will be considered as statistically significant.

---

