#### 3.2 SECONDARY OBJECTIVES

| Objectives                                                                                                                                                                                                                                                      | Outcome measures / Endpoints                                                                                                                                                                                                                        |
|-----------------------------------------------------------------------------------------------------------------------------------------------------------------------------------------------------------------------------------------------------------------|-----------------------------------------------------------------------------------------------------------------------------------------------------------------------------------------------------------------------------------------------------|
| Efficacy                                                                                                                                                                                                                                                 |                                                                                                                                                                                                                                                     |
| To assess the efficacy of the investigational therapy in patients with acute ischaemic stroke on the non-vitamin K antagonist oral anticoagulants with pre-stroke functional status of 0-1 points in mRS compared to placebo using modified Rankin Scale (mRS). | Proportion of patients with excellent functional status assessed with modified Rankin scale (mRS) (mRS 0-1) at 90 days (+/- 3 days) after investigational treatment administration.                                                                 |

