## 5 STUDY POPULATION

Previously functionally independent patients (0-2 points on the modified Rankin scale) taking one of the oral non-vitamin K antagonist oral anticoagulants (rivaroxaban, apixaban or dabigatran) as a prevention of cardioembolic and/or thromboembolic events, who despite maintaining adequate therapeutic anti-IIa/anti-Xa activity, which is directly proportional to the plasma NOAC concentration, have an ischemic stroke in the absence of another possibility of AIS specific treatment (i.e. primary mechanical thrombectomy treatment cannot be used – no occlusion of large cerebral/intracranial artery).

Detailed inclusion and exclusion criteria are provided in [Section 5.1](#) and 0 respectively. Patients who do not meet the eligibility criteria requirements for the STROACT study are described as screen failures; refer to [Section 5.4](#).

Prospective approval of protocol deviations to recruitment and enrolment criteria, also known as protocol waivers or exemptions, is not permitted.

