#### 6.5.1 VISIT 0 (PRE-TREATMENT) – SCREENING, ENROLMENT AND RANDOMISATION

The following examinations and procedures should be performed in the patient considered for enrolment and randomisation in the study:

1. Medical history with demographic information (obtained from the patient, his family, or the Emergency Medical Team responsible for patient's transfer to the hospital), including:
  - a. concomitant diseases and medications taken; it is important to determine when the last dose of the oral anticoagulant was taken
  - b. functional status prior to the current acute stroke (based on modified Rankin Scale [mRS])
  - c. the exact time of onset of symptoms of the current IS or the time when the patient was last seen without these symptoms
2. Verification of inclusion/ exclusion criteria.
3. ECG.  
**NOTE 1:** ECG must be performed once preferably within the first 24 hours from AIS but not later than 72 hours.
4. Physical examination.
5. Vital signs (BP and HR).
6. Signs and symptoms of infection(s).
7. Neurologic examination based on National Institutes of Health Stroke Scale (NIHSS).
8. Establishment of intravenous access (if not present yet); two are preferred for enrolled patients within groups B and C i.e., those on apixaban and rivaroxaban).

9. Collection of blood sample for the following lab tests:

- a. Anti-IIa activity for dabigatran or anti-Xa for rivaroxaban or apixaban or blood concentration of dabigatran.

NOTE 1: However, in patients on dabigatran, it is possible to enrol such a subject into the study based solely on a patient's or witness' report on the last intake of the anticoagulant ie, when it was administered within the last 24 hours preceding initiation of the study treatment. In these situations it is obligatory to collect and store blood for post-hoc anti-IIa testing. The procedure is described in the Laboratory Manual.

- b. Additional coagulation parameters: INR, APTT, fibrinogen
- c. Complete blood count (CBC) with platelet count
- d. Blood glucose concentration
- e. Biochemistry panel including electrolytes, serum creatinine (eGFR), CRP
- f. Troponin I concentration
- g. Transaminases (AlAT, AspAT) and bilirubin
- h. Albumin
- i. BNP/ NT-proBNP plasma concentration

10. Brain imaging – contrast-free CT scan (whenever possible with an assessment of the severity of early ischemic lesions preferably using the ASPECTS scale) or MRI (minimum requirements are DWI, SWI and FLAIR sequences, or equivalents).

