| 2.2                            | Odpowiedzialność wobec pozostałych członków rodziny:
Czy bieżący udar w sposób znaczący ograniczył (w porównaniu ze stanem wcześniejszym) zdolność pacjenta do opiekowania się własną rodziną?                                                                                                                                                                                                                                                                                                                                                                                                                                                              |  Tak (mRS = 2)
 Nie |
| 2.3                            | Życie towarzyskie i aktywności w czasie wolnym:
Czy bieżący udar ograniczył (w porównaniu ze stanem wcześniejszym) dotychczasowe regularne aktywności prowadzone w czasie wolnym od pracy o więcej niż o połowę?
Aktywności w czasie wolnym obejmują uprawianie hobby i realizację zainteresowań. Dotyczą zarówno aktywności wykonywanych poza domem (np. chodzenie do kawiarni, barów/pubów, restauracji, klubów, kościoła, kina, odwiedzanie przyjaciół, spacerowanie) oraz aktywności wykonywanych w domu (np. „aktywne” uczestnictwo, takie jak robienie na drutach, szycie, malowanie, granie w gry towarzyskie, czytanie książek, majsterkowanie). |  Tak (mRS = 2)
 Nie |
| 2.4                            | Ograniczenia wynikające z innych schorzeń lub ograniczeń fizycznych:
Czy zdolność do pracy zawodowej / nauki, opiekowania się własną rodziną lub aktywności prowadzone w czasie wolnym od pracy zostały w sposób znaczący zaburzone przez schorzenia lub ograniczenia fizyczne niezwiązane z udarem ?                                                                                                                                                                                                                                                                                                                                                       |  Tak (mRS = 2)
 Nie |

Zmiany jakie zaszły pomiędzy stanem sprzed udaru a chwilą obecną z odnotowaniem ich związku z udarem

---

---

---

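### The primary non-inferiority test ignores pre-stroke mRS, a collected baseline that strongly predicts Day 90 mRS 0-1, and so forgoes an available gain in power

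*Protocol*

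**What the plan says.** The primary analysis is set out in Protocol section 11.5.2.1 and repeated in 11.5.4. Each NOAC arm is analysed on its own, with two proportions, their difference and a confidence interval, followed by "One-sided noninferiority test with 15% margin for difference in proportions will be performed" and "A p value lower than 0.176 will be considered as statistically significant". No covariate or stratum enters the test. Section 11.5.4.1 applies one-sided 0.0238 to the same endpoint at the interim look.

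On pre-stroke function:

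- Section 5 describes the population as "Previously functionally independent patients (0-2 points on the modified Rankin scale"), and exclusion criterion 2 in section 5.2 removes only scores above 2. Pre-stroke mRS 2 is therefore eligible.
- Section 6.5.1 requires at Visit 0 "functional status prior to the current acute stroke (based on modified Rankin Scale [mRS"]). Section 11.5.1.2 uses Visit 0 mRS for a baseline table only.
- Sections 6.4 and 7.3.1 stratify randomisation by NIHSS alone.
- The form in section 14.2.2 has an item 2.4 headed "Ograniczenia wynikające z innych schorzeń lub ograniczeń fizycznych" (limits arising from other illnesses or physical limitations). A yes gives mRS 2. The form also says to choose the higher grade when in doubt.
- Section 3.2 has a secondary mRS 0-1 endpoint for patients "with pre-stroke functional status of 0-1 points in mRS compared to placebo".

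The primary endpoint in section 3.1 names both mRS 0-1 and mRS 0-2. The protocol does not say to which cut the test or the planning rate refers.

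**The concern.** A patient who enters with mRS 2 because of some other illness will normally still have that illness at Day 90. Item 2.4 then scores the patient 2 or worse whatever the treatment did, so such a patient can hardly count as an mRS 0-1 success in either group. Pre-stroke mRS thus explains part of the outcome variance before treatment starts, and the crude difference leaves that part in the error term.

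This is more than detail left to the SAP, because section 11.5.2.1 already fixes the estimator, interval level, margin and threshold. The protocol also specifies adjustment elsewhere: age for secondary endpoints (11.5.2.2) and the baseline score for exploratory scales (11.5.2.3). At stake is precision in three separate small comparisons, each planned at only 70% power.

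**Working it through.** **1. The plan's own figure.** Section 11.3 gives 40% success in both groups, a 15-point margin, "One sided significance level 0.2", 70% power, one interim look and 10% dropout.

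n = 2(0.4)(0.6)(z₀.₈ + z₀.₇)² / 0.15² = 0.48 × (0.8416 + 0.5244)² / 0.0225 = 39.8, so 40.

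Hwang-Shih-DeCani spending with γ = −4 spends 0.0238 at half information, which matches section 11.5.4.1. It inflates n by 1.006: 39.8 × 1.006 = 40.05, so 41. With dropout, 41/0.9 = 45.6, so 46. The stated 46 per group reproduces for an unadjusted test.

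**2. Variance removed by pre-stroke mRS (mRS 0-1 cut).** Assumptions not in the protocol: a share s has pre-stroke mRS 2 and none of them reaches 0-1. The overall rate is kept at the planned 40%, so the rate among the others is p₁ = 0.40/(1 − s). Within-stratum variance relative to crude variance is (1 − s)p₁(1 − p₁)/0.24 = (1 − p₁)/0.6.

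**3. Power at the final look, no true difference.** There are 41 evaluable per group and the one-sided threshold is 0.176, so z = 0.9307. Power = Φ(0.15/SE − 0.9307), with SE = √(0.48 × ratio/41). The formula and a simulation of the same look give:

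| s | p₁ | Variance ratio | SE | Power by formula | Simulated power |
|---|---|---|---|---|---|
| crude test | – | 1.000 | 0.1082 | 67.6% | 69% |
| 10% | 0.444 | 0.926 | 0.1041 | 69.5% | 70% |
| 20% | 0.500 | 0.833 | 0.0988 | 72.2% | 72% |
| 30% | 0.571 | 0.714 | 0.0914 | 76.1% | 76% |

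The simulated crude power is about 69% at every s. A two-look normal approximation with 41.4 evaluable per group (46 × 0.9) gives the same pattern: 68.1% crude against 70.1%, 72.7% and 76.6%. The crude figure lies just under 70% because of the 0.176 final threshold, not because a covariate is missing.

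**4. A softer floor.** If 5% of the mRS 2 patients do reach 0-1, the two-look figures become 69.6%, 71.6% and 74.4%, still against 68.1% crude.

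**5. What adjustment does not change.** Suppose the true deficit is 15 points among patients able to reach 0-1. Overall it is 15 × (1 − s): 13.5, 12.0 and 10.5 points. The chance of declaring non-inferiority (two-look approximation) is then:

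| s | Crude | Stratified by pre-stroke mRS | Pre-stroke 0-1 only | Power of restricted test, no difference |
|---|---|---|---|---|
| 0 | 18.0% | 18.0% | 18.0% | 68.1% |
| 10% | 22.1% | 22.2% | 18.0% | 64.9% |
| 20% | 26.5% | 27.3% | 18.0% | 61.8% |
| 30% | 31.4% | 33.6% | 18.0% | 59.2% |

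Simulation of the final look agrees. At s = 20% it gives about 28% crude, 27% stratified and 18% restricted.

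**The case against.** The strongest objection is that the design is adequate as planned. The sample size was computed for a crude test, it reproduces, and nothing falls short because a covariate is absent. That stands: this is a forgone gain. Its size rests on a share that the protocol does not give, and at 10% it is about one point.

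The floor also belongs to the mRS 0-1 cut. Patients with pre-stroke mRS 2 can reach mRS 0-2, so none of the figures above carries over to that cut. And item 2.4 concerns conditions unrelated to the stroke, so a pre-stroke mRS 2 left by an earlier stroke may be scored differently. For that reason the floor is practical rather than absolute.

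Two stronger readings are tempting. A reader might infer that omitting the covariate causes a true deficit to be diluted. It does not. Dilution comes from who is analysed and where the scale is cut, and an adjusted risk difference still averages in the patients who cannot respond (step 5). A reader might also count chance imbalance as a separate harm: at s = 20%, a 10-point imbalance in the mRS 2 share moves the crude difference by 0.10 × 0.50 = 5 points. But the standard deviation of that imbalance is √(2 × 0.2 × 0.8/41), about 9 points. It is ordinary sampling variation already inside the crude variance, and so the power point seen from another side.

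The restricted secondary endpoint and the baseline table partly address the matter. However, section 11.5.2.2 gives the secondary endpoint a 95% interval, odds ratios and a 0.05 threshold, with no margin, so it does not serve as a non-inferiority check.

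**Conclusion.** The point holds as one of efficiency. The stated primary test leaves out a baseline that is already collected, is not balanced by design and strongly predicts the mRS 0-1 outcome. For that cut, at p<0.176 and 41 evaluable per group, adjustment would raise power from about 69% to about 70%, 72% or 76% at assumed pre-stroke mRS 2 shares of 10%, 20% or 30%. This assumes that none of those patients reaches 0-1 and that the overall rate is 40%; the gain is smaller if some do reach it.

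The documents support neither a claim that the trial is underpowered for this reason, nor a claim that adjustment would cure dilution, nor an extension to mRS 0-2. Dilution is real for mRS 0-1 but needs its own remedy. The change is worth making because it costs almost nothing; it is not essential to the validity of the test.

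**What to change.** In sections 11.5.2.1, 11.5.4 and 11.5.4.1, state that within each NOAC arm the 15-point margin is tested, at both looks, on a risk difference stratified or standardised by pre-stroke mRS (0-1 versus 2). Mantel-Haenszel weighting, or a logistic model with standardisation and a robust variance, would serve. Include the NIHSS randomisation stratum as well where cell sizes allow. Keep the crude difference as a supportive analysis and show the number with pre-stroke mRS 2 by treatment group beside the mRS 0-1 result.

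Separately, analyse mRS 0-1 in patients with pre-stroke mRS 0-1, already a secondary endpoint, against the same 15-point margin as a supporting non-inferiority analysis. Its power is lower (about 65%, 62% or 59% at shares of 10%, 20% or 30%), so it should support the primary test rather than replace it.

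The cost is protocol and SAP wording plus a little programming, with no new data. The downside is sparse strata within an arm, especially at the interim look. Fix in advance a rule for dropping the NIHSS stratum if cells are too small.
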